### Implementation {16c}

An independent person generates the allocation sequence and prepares and keeps the sealed envelopes. The main investigator will obtain the next sealed envelope from this person after informed consent was given. The note of allocation (treatment or control) and the numbered envelope are attached to the informed consent form. The main investigator then informs the participant about allocation. Allocation to a specific therapist depends mostly on the therapists’ schedules and timing of enrollment.

## Assignment of interventions: blinding

### Who will be blinded {17a}

Blinding to treatment is impossible for both participants and therapists. Treatment allocation is not discussed with the research assistant who gathers the data from the online tool (Exploratio), unless circumstances demand it. For example, the timing of questionnaires has to be changed when a treatment session was missed. The statistician engaged to perform the analysis is blinded to treatment allocation.

### Procedure for unblinding if needed {17b}

Not applicable, because blinding to treatment is impossible in the first place.

### Plans to promote participant retention and complete follow-up {18b}

In the first conversation on the telephone, the principal investigator establishes a positive atmosphere, in which the candidate feels free to ask questions and discuss any misgivings they might have. After the candidate has decided to participate, the investigator relates the particulars about data collection. Content (diary questions), timing, and the limited time required to fill out the questions/questionnaires of assessment are discussed. Participants are also informed that they will receive a reminder (by telephone call) from the research assistant when the diary questions or questionnaires are not filled out by a specific time in the evening. This specific time is chosen in agreement with the participant. The investigator notifies the participant that an evaluation interview will take place after data collection, in which study participation will be reviewed, and participant’s wishes concerning further treatment will be discussed. Also, participants are informed that they will receive a compensation of €25 when all questions and questionnaires have been filled out, and that participants in the treatment condition will receive a contribution for their travel costs of €6 for each visit.

The principal investigator encourages the participant to contact her with any questions or difficulties they might have filling out the diary questions or questionnaires.

When a participant has forgotten to answer the diary questions, or to fill out the questionnaires, the research assistant calls them and kindly reminds them of the e-mail, and asks them to fill out the questionnaire. A friendly atmosphere in these calls is essential.

### Data management {19}

Each participant will be allotted a unique ID number. The data from the diary questions and questionnaires are gathered using a secure connection and are stored in an online, password-protected, secured database that is only accessible by the researchers. The data are extracted and saved to the research archive coded with the unique identification number, first in their original format (separately for each participant and each day), and after that data are imported to the overall data collection file in Excel. The original format files serve as a backup. The data will be monitored for consistency and validity (e.g., check for errors, range checks, missing values) at collection by the research assistant and later by the principal investigator. The overall data file will be exported to the statistical analysis program.

Any other data will be stored under the identification number only. The coding list with identification numbers and names and the informed consent forms will be kept separate and secured by the principal investigator.

Data from diary questions, questionnaires, and treatment sessions’ video footage will be kept for 15 years, and patient files (intervention group) will be kept for 20 years in accordance with national law. Modifications to this protocol will be submitted to the approving ethical committee and the institutional review board.

### Confidentiality {27}

See {19}.

### Plans for collection, laboratory evaluation, and storage of biological specimens for genetic or molecular analysis in this trial/future use {33}

No biological specimens are gathered in this study.

## Statistical methods

### Statistical methods for primary and secondary outcomes {20a}

The statistical analyses will be performed according to the intention-to-treat principle.

The primary outcome measure in this study is the reported intensity of abdominal pain, which is registered during 14-day periods of daily diary questions, at three points in time, yielding 42 data points per participant.

The principal research question will be answered by performing a linear mixed effect models analysis, based on 2 groups (treatment and control) and 3 (baseline, after treatment, follow-up) × 14 (days) measuring moments. Before the analysis, data will be checked for outliers and the assumption of linear relations. Values with an absolute *z*-score > 4 will be treated as outliers and removed.

The model will be built in a stepwise model, first fitting an intercept-only linear mixed effects model, allowing to disentangle variance between patients and variance within patients over time. In a second step, the predictor time will be added, to control for any unexplained changes over time in subsequent models. If necessary, a quadratic term for time will be added to the model as well. Subsequently, in the third model, the fixed effect for condition will be added. In the fourth model, the fixed effect for measurement period (baseline, treatment, and follow-up) will be added (note, this variable will represent the difference between baseline and treatment period and baseline and follow-up period irrespective of condition). In the sixth model, the difference between measurement periods will be allowed to vary over patients (a so-called random slope for measurement period). If this is significant, in a seventh model, an interaction between measurement period and condition will be included, to explain why the differences between periods vary over patients. This last term, the interaction between measurement period and condition, answers our primary research question: what is the overall difference in changes in pain score over measurement periods between condition and control group?

After performing the analysis, the assumption of normally distributed errors for both level 1 and level 2 errors will be assessed.

As to the secondary outcome measures: the data gathered from the residual diary questions (pertaining to other IBS symptoms and hindrances experienced in valued activities) are analyzed in the same way as the primary outcome (abdominal pain intensity).

The outcome measures from the two standardized questionnaires, which only yield 3 data points, will be analyzed by LME models based on 2 groups (treatment and control) and 3 measuring moments (at baseline, after treatment, and at follow-up). See Fig. 2.

For all analyses regarding symptom improvement, a one-sided significance threshold of alpha = 0.05 will be used. For all other analyses, a two-sided* p* value of 0.05 will be used as the significance threshold. We will report both *p*-values and 95% confidence intervals.

Based on the Adequate Relief Question, and based on the presence of a clinically relevant reduction of symptoms as measured by the IBS-SSS, a Number Needed to treat will be calculated, for two measuring moments: after treatment and at follow-up.

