### Outcomes {12}

The primary outcome of this study is the intensity of abdominal pain. As the intensity of abdominal pain in IBS can vary greatly from day to day, we have chosen to pose the same question each day for 2 weeks. Participants answer the question: “How much did you suffer from abdominal pain during the last 24 h?”. The subject’s answer is given on a 21-point Likert scale (0 = no pain, 10 = worst pain imaginable, half points possible).

In addition to the primary outcome measure (abdominal pain), we pose four other diary questions at the same time, during the same period, with the same 21-point Likert scale. Based on their statements at inclusion about their principal IBS symptoms, we ask about their top two symptoms (abdominal pain excluded): “How much did you suffer from (complaint) during the last 24 h?” (0 = not at all, 10 = extreme suffering, half points are possible). These symptoms could be frequently occurring IBS symptoms such as diarrhea, constipation, and bloating, but they can also be more idiosyncratic such as dizziness. We also ask about the hindrance subjects have experienced from their IBS symptoms when engaging in everyday activities. Based on their statements at inclusion about the two- valued activities that are most impeded by the IBS symptoms, we ask for every one of these activities: “How much hindrance have you experienced from your IBS symptoms when engaging in this activity?” (0 = no hindrance at all, 10 = made completely impossible; half points possible). Activities most likely to be impeded by IBS symptoms are working, doing sports, going out for dinner, and going out (dancing, theatre, etc.).

The 14-day-sequence of these 5 “diary questions” is administered at inclusion, 8 weeks after inclusion (for the intervention condition this means after treatment), and at follow-up (20 weeks after inclusion, 3 months after treatment).

In addition to the diary questions, we administer several questionnaires, the purpose of which is to describe the population and to either confirm or disconfirm the results of the diary questions. They also enable comparing outcomes with those of other studies. The questionnaires are administered on the last day of every 14-day-sequence of diary questions.

The questionnaires administered are:IBS-SSS (Irritable Bowel Syndrome—Severity Scoring System) [35].

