### Sample size {14}

Several factors have influenced the sample size in this study: setting, method of analysis, and the estimate of comparability with previous scientific research.

As the study is conducted as part of the curriculum of a training course taken by the principal investigator, both time and resources are limited. Our aim is to demonstrate a clinically relevant treatment effect regarding the primary outcome measure with a limited sample size.

The design of our study enables us to analyze our primary outcome data (pain score diary) using a linear mixed effects models analysis. Sample size was computed using the online statistical calculation program GLIMMPSE (General Linear Mixed Model Power and Sample Size): https://glimmpse.samplesizeshop.org/#/ using an alpha of 0.05 and a desired minimum power of 0.80.

The most important estimated value required by the GLIMMPSE program is the expected effect size. Since a study on the effect of EMDR on abdominal pain in IBS has never been done before, a search was made for comparable research. A review on EMDR treatment for chronic pain found large effect sizes [22]. The EMDR for phantom limb pain study design is most comparable to our study design [28]. Based on this study, a remarkably large effect size d of 1.22 was calculated. On entering this effect size, GLIMMPSE calculated that a sample size of 12 should be sufficient. However, when a demonstration of an average effect size is wanted, a sample size of 24 is needed. This sample size is adequate to analyze the primary outcome measure daily pain scores using a linear mixed effects model. In addition, this sample size is also expected to be adequate to analyze the secondary outcome measures from the standardized questionnaires (measures taken only three times in total) with LME models. Taking drop-out into account we decided to include a maximum of 34 participants.

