### Methods in analysis to handle protocol non-adherence and any statistical methods to handle missing data {20c}

Every effort is made to avoid missing data. The way the diary questions and questionnaires are administered online makes it impossible to skip a question. Also, patients who do not complete a questionnaire or diary will receive one or more reminders.

For all analyses, a linear mixed effects model (LMEm) analysis is used. The advantage of linear mixed effects modeling is that the analysis can be performed on all data available, and missing data is handled automatically assuming Missing at Random (MAR) without requiring imputations.

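### The |z| > 4 rule deletes permissible diary ratings because of their size, without an error check or a stated reference; it is usually inert, and any bias can go either way

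*Protocol article*

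**What the plan says.** All of this is in the protocol article.

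- **Statistical methods {20a}**: "Before the analysis, data will be checked for outliers and the assumption of linear relations". The rule for the absolute z-value follows: "score > 4 will be treated as outliers and removed". So it acts on raw values, not on residuals. The section does not say whether z is pooled or taken per period, arm or person. It asks for no confirmation of an error and names no analysis with the values kept. The analysis is to follow intention to treat, and the other four diary items are analysed like the pain item.
- **Outcomes {12}**: pain is rated on a 21-point scale ("0 = no pain, 10 = worst pain imaginable, half points possible"). Daily rating is justified in these words: "As the intensity of abdominal pain in IBS can vary greatly from day to day".
- **Data management {19}**: the data are checked for errors, range and missing values.
- **Missing data {20c}**: the mixed model is preferred because "the analysis can be performed on all data available", under missing at random.
- **Volume of data**: {20a} has the diary run "at three points in time, yielding 42 data points per participant", and in Sample size {14} "we decided to include a maximum of 34 participants".

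**The concern.** An outlier rule on raw data helps if it catches impossible values. Here the scale has fixed ends and a range check exists, so an impossible value is caught without it. What remains for the rule is ratings that a patient could have given. They are dropped because they are far from a mean, with no evidence that they are wrong.

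Two stated principles are affected. Under missing at random, whether a value is missing must not depend on that value given the observed data; here it does, by construction. Intention to treat also sits badly with discarding valid outcome data from randomised patients. With at most 34 participants, one patient's lost days can show in the estimate of the primary outcome.

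**Working it through.** **Inputs from the article.** 3 periods × 14 days = 42 values per participant, as stated in {20a}; 34 × 42 = 1,428 values in total; scale 0 to 10; cutoff 4. No diary mean or SD is given, so every mean, SD and responder count below is an assumption.

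**1. Reach of the rule with one common mean m and SD s.** A 0 is removed only if m/s > 4, that is s < m/4. A 10 is removed only if s < (10 − m)/4.

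| Mean | 0 removed if SD below | 10 removed if SD below |
|---|---|---|
| 6 | 1.50 | 1.00 |
| 7 | 1.75 | 0.75 |
| 8 | 2.00 | 0.50 |

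With a high mean, the low tail is the one realistically in reach.

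**2. Pooled z with k patients at 0 on all 28 post-baseline days.** Their share of the values is q = 28k/1428 = k/51. If the other values have mean m and SD s, the condition mean > 4 SD reduces to s < (m/4)·√(1 − 17q) = (m/4)·√(1 − k/3).

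- k = 1: s below 1.22 (m = 6) to 1.63 (m = 8).
- k = 2: s below 0.87 to 1.15.
- k = 3 or more: never.

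This agrees with the one-sided Chebyshev limit: at most 1/17 of the values, 84 of 1,428, can lie beyond 4 SD in one tail.

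**3. Settings where nothing happens.**

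- z within person and period (n = 14): the largest possible |z| is 13/√14 = 3.47.
- The minimal entry pattern (pain of 6 on half the days, 0 on the rest): mean 3, SD 3.11, so z of a 0 is −0.96.
- Simulated trials with between-person SD 1.0 and within-person SD 1.5: pooled z removes none with 1, 2 or 5 full responders.

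**4. Settings where it acts against EMDR** (simulated, 17 per arm; effect is the EMDR-minus-control change at post-treatment).

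- Pooled z, baseline mean 7.5, between/within SD 0.7/1.0, one responder at about 0.3: about 24 of that patient's 28 values go, and the effect moves from −0.68 to −0.56.
- Pooled z, baseline mean 6.5, SDs 0.5/1.0, one responder: about 17 of 28 go, and the effect moves from −0.62 to −0.59.
- z against the baseline mean and SD, SDs 0.5/1.0, five responders: nearly all of their 5 × 28 = 140 values go, and the effect moves from −1.90 to −0.51.
- The same baseline reference with mean 6.5, between-person SD 1 and 20% responders falling by 5.5 points: about 41 to 47 values go at within-person SD 1, about 2 at SD 1.5 and none at SD 2.

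The estimates after deletion are rough, because they depend on the weight given to a patient with few days left. In the first case the most that can be lost is that patient's whole contribution, (7.5 − 0.3)/17 = 0.42 points.

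**5. A setting where it acts in favour of EMDR.** Take z per arm and period: 17 × 14 = 238 values with mean 1.5 and SD 1.0, three of them replaced by flare days of 7, 8 and 7. The mean becomes 1.5 + 17.5/238 = 1.57. The variance becomes about 0.99 + 102.75/238 − 0.01 = 1.41, so the SD is 1.19. The cutoff is 1.57 + 4 × 1.19 = 6.33, and all three flare days go. This lowers the EMDR mean by about 0.07.

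**6. Other cases.** With z over one person's 42 days, a patient stable near 7 (values 6.5 to 7.5) who has one day at 2 has z = −5.6 for that day and loses it, although no response is involved. For a secondary item that is 0 on most days and takes one fixed value on a share f of days, z of that value is √((1 − f)/f). This exceeds 4 when f < 1/17, and then every symptomatic day is removed.

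**The case against.** **The rule hardly ever acts.** This stands for most plausible settings. The article itself describes large day-to-day variation, which points to the inert case. It limits the size of the problem; it does not give the rule a use.

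**The z reference may be defined in the full protocol or an analysis plan.** It may, and a missing definition alone would be no finding in a condensed article. The point rests on what the article does state: removal of raw values by size, without verification.

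**In-range errors can occur.** True: a mis-click is possible, and daily files are imported into Excel. But distance from a mean does not separate an error from a bad or a good day. Checking against the original files does.

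**The statistician is blinded.** This limits deliberate choice of a reference, but it does not make deletion by outcome valid.

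Some stronger readings are tempting but not supported:

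- *The rule removes the best responders and so shrinks the effect.* This needs a narrow spread that the article does not report, and either one or two exceptional responders (pooled z) or a baseline reference that the article does not mention. Other references are inert or push the other way.
- *The sample is selected for stable high pain.* Eligibility criteria {10} ask for pain on only 5 of 10 days, and the threshold of 60 is on the IBS-SSS item, not the diary.
- *The article promises to keep every value.* The sentence in {20c} describes what the model can do with incomplete data. The clearer tension is with missing at random.

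**Conclusion.** The concern holds as a minor but real defect in a stated rule for the primary outcome and the other diary items. The rule adds nothing to the range checks against impossible values. Whatever it removes beyond them is a permissible rating, dropped for its size, and the direction of any bias depends on an unstated reference.

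The expected effect is near zero in most plausible settings. In the assumed narrow samples with pooled z and a lone full responder, the shift was 0.03 to 0.12 points on the 0–10 scale, with a ceiling of 0.42 in the second of these. Only baseline-referenced z combined with a narrow spread gives a large distortion. These sizes rest on assumed SDs and responder numbers. The limits s < m/4, 3.47 and 1/17 need no such assumption.

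**What to change.** Replace the outlier sentence in Statistical methods {20a} with:

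> All in-range diary values are kept in the primary and secondary analyses; only verified entry or transfer errors are corrected.

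Add that extreme residuals and influential patients will be examined after the model is fitted, with any refit without them reported as a sensitivity analysis.

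The cost is one changed sentence and slightly more analysis work. No data collection changes.

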### Methods for additional analyses (e.g., subgroup analyses) {20b}

If the collected sample size allows it, it will be investigated whether observed differences between patients in treatment effect can be explained by other variables such as sex, age, symptom severity at baseline, the severity of PTSD-related symptoms at baseline, and the number of other ongoing treatments (such as diets, etc.).

In describing the study population, the following data will be reported:The frequency of reported IBS symptoms and valued activities (as reported at initial screening).The percentage of patients that meet the criteria for PTSD (as determined by LEC-5 and PCL-5 results).Average and standard deviation scores on PCL-5, per group and per measuring moment.The number of patients that have experienced additional traumatic experiences during the time of participation.

Chi-square tests or *t*-tests will be done to test for a priori differences between the intervention and control group regarding demographic and descriptive values. Both *p* values and standardized differences will be reported.

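### The primary model gives each arm its own baseline mean and reads the effect as a difference in change: valid, but less precise than baseline adjustment at moderate correlations in a trial capped at 34

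*Protocol article*

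**What the plan says.** The section on statistical methods for primary and secondary outcomes {20a} of the Protocol article lists the primary model term by term. The outcome is diary pain, "which is registered during 14-day periods of daily diary questions, at three points in time, yielding 42 data points per participant". After the intercept and time comes condition: "Subsequently, in the third model, the fixed effect for condition will be added". Baseline then enters as a level of the response: "In the fourth model, the fixed effect for measurement period (baseline, treatment, and follow-up) will be added". A random slope for period follows, then the interaction: "This last term, the interaction between measurement period and condition, answers our primary research question". That question is worded as "what is the overall difference in changes in pain score over measurement periods between condition and control group".

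No step adds baseline pain as a covariate or holds the arms to a common baseline mean. Baseline severity appears only under additional analyses {20b}, in a list ("sex, age, symptom severity at baseline, the severity of PTSD-related symptoms at baseline", among others) of possible explanations for differences in treatment effect, to be examined if numbers allow.

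The scores of the two standardised questionnaires "will be analyzed by LME models based on 2 groups (treatment and control) and 3 measuring moments". Nothing further is said about how baseline enters those models.

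**The concern.** With condition, period and their interaction all in the model, each arm has its own free mean in each period. The condition term becomes the arm difference at baseline, and the interaction becomes the difference in change from that baseline. Randomisation makes the baseline means equal in expectation, so estimating a separate baseline difference spends information on a quantity known to be zero on average.

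This matters because precision cannot be bought with patients. Sample size {14} says that time and resources are limited, puts the need at 24 and caps inclusion at 34. Recruitment {15} reports that the first estimate of eligible patients was too optimistic. Sequence generation {16a} describes 1:1 allocation by a spreadsheet function and no stratification on pain, so a chance imbalance at baseline is a realistic prospect.

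**Working it through.** **The plan's own figure.** The article gives no precision figure for this choice. Its sample sizes (12, 24, 34) were obtained "using an alpha of 0.05 and a desired minimum power of 0.80". They cannot be reproduced, because the within-patient correlation, the variances, the size of the average effect and the sidedness used are not stated. The argument below does not depend on them.

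**Inputs.** From the article: 2 arms at 1:1, 14 days × 3 periods, N between 24 and 34, one-sided alpha 0.05 for symptom improvement. Assumed: r, the correlation between a patient's baseline and later 14-day means, over 0.3 to 0.9, and equal variance σ² of those means in each period.

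**Step 1: what the interaction estimates.** The arm-by-period means are saturated, so with complete data the interaction at each later period equals (later minus baseline, EMDR) minus (later minus baseline, wait list). Random effects and common time terms do not alter this.

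**Step 2: large-sample variances, n per arm.**
- Difference in change: (2/n) × 2σ²(1 − r)
- Baseline-adjusted: (2/n) × σ²(1 − r²)
- Ratio, adjusted to change: (1 + r)/2

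Without equal variances (σ0 at baseline, σ1 later), the change-score variance exceeds the adjusted one in proportion to (σ0 − rσ1)², which is never negative.

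Check on the full 42-observation mixed model (17 per arm, assumed variances giving r = 0.486): variance 0.231 with a common baseline mean and 0.311 with the condition main effect. The ratio is 0.743, and (1 + 0.486)/2 = 0.743.

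**Step 3: small-sample cost.** Estimating the covariate slope inflates the adjusted variance by about 1 + 1/(N − 4): 1 + 1/30 = 1.033 at N = 34 and 1 + 1/20 = 1.05 at N = 24. Simulation (20,000 runs on 14-day means) agrees with this:

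| r (assumed) | (1 + r)/2 | Simulated ratio, N = 34 | Simulated ratio, N = 24 |
|---|---|---|---|
| 0.3 | 0.65 | 0.67 | 0.69 |
| 0.5 | 0.75 | 0.78 | 0.79 |
| 0.7 | 0.85 | 0.88 | 0.89 |
| 0.9 | 0.95 | 0.98 | 1.00 |

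Break-even at N = 24: (1 + r)/2 × 1.05 = 1 gives r = 2/1.05 − 1 ≈ 0.905.

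**Step 4: power, one-sided 0.05, at an assumed d = 0.8** (in SDs of a 14-day mean), change score against adjusted:

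| r (assumed) | N = 34 | N = 24 |
|---|---|---|
| 0.3 | 0.61 vs 0.76 | 0.48 vs 0.62 |
| 0.5 | 0.74 vs 0.83 | 0.60 vs 0.69 |
| 0.7 | 0.90 vs 0.93 | 0.78 vs 0.83 |

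**Step 5: chance imbalance.** Under simple randomisation the baseline difference D, in SDs, has standard error 2/√N: 0.343 at N = 34 and 0.408 at N = 24. The chance that |D| exceeds 0.3 is about 38% and 46%. Given D, the change-score estimate is displaced by (1 − r)D in absolute size. With D = 0.3 and r = 0.5 that is 0.5 × 0.3 = 0.15 SD.

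**Step 6: order of baseline and disclosure.** Concealment {16b} opens the envelope after consent, and implementation {16c} has the investigator then tell the participant the result. Outcomes {12} places the first diary fortnight only at inclusion. Participant timeline {13} puts intake the day after the questionnaires, which close that fortnight. The text therefore does not show whether the baseline diary comes before or after disclosure, and the flow figures are not available here.

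**The case against.** The strongest defence is that nothing here is wrong. The hypothesis concerns a greater reduction in pain, the planned term estimates exactly that, and the estimator is valid. Covariate adjustment is also often left to an analysis plan. The first part stands: this is an improvement in efficiency. The second does not remove the point, because the article fixes the primary model term by term, so the separate baseline means are a stated choice.

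The range of r matters too. Averaging 14 days makes the period means more reliable, so r may be high. If the 24 is a total and the analysis a change score, 80% power needs r of about 0.71 to 0.78 at an assumed d = 0.8, or 0.89 to 0.92 at d = 0.5. In the upper range little or nothing is gained.

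A reader might infer more than the text supports:
- **That the planned estimate is biased.** It is not. A chance imbalance displaces a single trial's estimate, but it averages out over randomisations and is already reflected in the standard error.
- **That regression to the mean contaminates the effect.** Both arms pass the same entry threshold, so it cancels in expectation.
- **That adjustment is always at least as precise.** That is a large-sample statement. At N = 24 the advantage is gone near r = 0.9.
- **That the questionnaire models share the fault.** The article does not say how baseline enters them, and its wording is compatible with a common baseline mean.

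The timing objection also stands. If patients knew their allocation while completing the baseline diary, equal baseline means are no longer guaranteed, and imposing them could introduce bias. The planned change score is not protected in that case either, since it carries the affected baseline at full weight.

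**Conclusion.** The point holds as one of efficiency. The primary analysis uses a valid estimator that forgoes precision available from data the trial already collects, and it leaves the estimate exposed to chance baseline imbalance. At N = 34 baseline adjustment would cut the variance by about 33%, 22%, 12% and 2% at r = 0.3, 0.5, 0.7 and 0.9. At N = 24 the cuts are about 31%, 21%, 11% and nil. At r = 0.5 an adjusted analysis of 34 patients is worth about 34/0.78 ≈ 44 analysed as change scores, and one of 24 about 24/0.79 ≈ 30.

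These figures rest on assumed r, equal variances across periods and complete diaries, and they apply to the diary mean as covariate. With missing diaries the interaction is only approximately the raw difference in change, but the arms still have separate baseline means. The figures do not carry over to the screening pain score, whose correlation with the diary means is unknown.

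**What to change.** State when the baseline diary is completed relative to disclosure of allocation, then pre-specify one of the following.

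- **Baseline diary completed before disclosure.** For pain and the other diary outcomes, use either of two models. One is a constrained longitudinal model: common baseline mean, period effects, period × condition at the two later periods only, and the patient-level random effects for period retained so that the correlation between periods is modelled. The other takes the later periods as the response, with each patient's 14-day baseline mean as covariate.
- **Allocation disclosed before the baseline diary.** Do not impose the equal-baseline constraint. Use the screening IBS-SSS pain score, collected before consent, as covariate. Its gain is unknown and probably smaller, because eligibility restricts that score to 60 or more.

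State the same baseline adjustment for IBS-SSS and IBS-QOL, under the same timing condition, since their baseline is taken on the last day of the baseline fortnight.

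The cost is one line of model wording and about one degree of freedom, with no new data. The research question is unchanged, because both analyses target the same effect. The article reports recruitment as ongoing and plans no interim analysis, so on its account the change can be made before outcomes are examined.
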